### Sample size

Previous population-based data from the Singapore Epidemiology of Eye Diseases (SEED) study reported an incidence of progression to late AMD of 0.51% among adults aged ≥40 years [10]. However, a higher progression rate is anticipated in the present study, as participants aged ≥55 years will be recruited.

The target sample size of 1,500 participants was selected to investigate progression to late AMD in an Asian community-based cohort. This sample size was determined based on feasibility and anticipated recruitment and 5-year follow-up capacity.

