	Complete RPE and outer retinal atrophy (cRORA)	(1) a region of hypertransmission of at least 250 µm in diameter, (2) a zone of attenuation or disruption of the RPE of at least 250 µm in diameter, (3) evidence of overlying photoreceptor degeneration, and (4) absence of scrolled RPE or other signs of an RPE tear
OCTA		• Choroidal vascularity index (CVI) • Choriocapillaris flow area Those variables will be measured by the DREAM OCT in-built software and the average values at Early treatment diabetic retinopathy study (ETDRS) 0–1, 0–3, 0–6 mm areas will be documented. Abnormal flow signal in the outer retina/sub-RPE space or neovascular network visible on en-face view of those slabs

* These variables will be graded just in late AMD stage

The primary study outcome will be progression to late AMD, defined as 1- neovascular AMD (the development of macular neovascularization (MNV)) and/or 2- Geographic atrophy (GA, defined as atrophy lesions seen on CFP and FAF and further confirmed by the presence of complete retinal pigment epithelium and outer retinal atrophy (cRORA) on OCT, in the absence of present or previous MNV), during follow-up.

The rate of progression to late AMD will be reported, with event time assigned to the first visit at which GA or MNV is detected. The rate and time to event of progression from non-exudative neovascular AMD, detectable abnormal flow signal in the outer retina/sub-RPE space on OCTA and no exudative sign or macular fluid on OCT imaging, to exudative neovascular AMD will also be reported.

The prevalence of each multimodal imaging biomarkers alongside the rate of quantitative biomarkers and their longitudinal changes will be reported. By integrating those biomarkers with clinical (medical, drug and social history), genetic, and metabolomic data, we will assess their relative risk for progression and will present potential predictors. Furthermore, the identified prognostic factors may be used to explore clinically meaningful risk strata and inform the development of an AMD staging framework tailored to the Asian population. Using that classification, the rate of progression to different stages of AMD through years of follow-up will be reported.

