### Statistical methods

Descriptive statistics will be used to summarize baseline demographic, systemic, ocular, and imaging characteristics of the study cohort. Continuous variables will be presented as mean ± standard deviation (SD) for normally distributed data, or median and interquartile range (IQR) for non-normally distributed data. Categorical variables will be summarized using frequencies and percentages. Normality will be assessed using histograms and the Shapiro–Wilk test.

All analyses will primarily be performed at the eye level. As both eyes from a participant may be included, inter-eye correlation will be accounted for using generalized estimating equations (GEE) or mixed-effects models where appropriate.

Because AMD progression will be assessed at scheduled study visits rather than continuously observed, the primary analysis will evaluate progression to late AMD over predefined follow-up intervals using discrete-time survival models. Standard Cox proportional hazards models may be performed as sensitivity analyses. Where appropriate, interval-censored survival models will be explored.

Variables considered for multivariable models may include demographic factors, systemic risk factors, smoking history, and multimodal imaging biomarkers, including drusen characteristics, pigmentary abnormalities, subretinal drusenoid deposits, hyperreflective foci, drusen volume, double-layer signs, OCTA flow abnormalities, and choroidal parameters. Hazard ratios (HR) and 95% confidence intervals (CI) will be reported.

Longitudinal continuous imaging parameters, including drusen volume, retinal thickness, and choroidal thickness, will be analyzed using linear mixed-effects models to account for repeated measurements over time and within-subject correlation. Logistic regression analyses may additionally be performed for binary outcomes such as conversion to late AMD within predefined follow-up intervals.

Where appropriate, exploratory multivariable models integrating these biomarkers may be constructed to investigate risk stratification. All statistical analyses will be performed using R software (R Foundation for Statistical Computing, Vienna, Austria) and/or IBM SPSS Statistics (IBM Corp., Armonk, NY, USA). All statistical tests will be two-sided, and a p-value <0.05 will be considered statistically significant.

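### Predictors, a new staging scheme and its progression rates would come from one cohort with few late-AMD events, with p<0.05 for every test and no correction for optimism stated

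*Protocol article*

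**What the plan says.** All references are to the protocol article.

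- *Sample size* cites earlier population data that "reported an incidence of progression to late AMD of 0.51% among adults aged ≥40 years". It does not say over what period. It adds that "a higher progression rate is anticipated in the present study, as participants aged ≥55 years will be recruited", without a figure. On the choice of 1,500: "This sample size was determined based on feasibility and anticipated recruitment and 5-year follow-up capacity".
- *Statistical methods* makes discrete-time survival models the primary analysis and gives a candidate list: "Variables considered for multivariable models may include demographic factors, systemic risk factors, smoking history, and multimodal imaging biomarkers". Eight imaging items are then named. The rule for all tests is that "a p-value <0.05 will be considered statistically significant". The models that integrate biomarkers for risk stratification are described as exploratory.
- *Grading of retinal imaging and outcomes to be measured* adds genetic and metabolomic data to the search for predictors. It says the factors found may be used to explore risk strata and inform an Asian staging framework. The next sentence is firm: "Using that classification, the rate of progression to different stages of AMD through years of follow-up will be reported".
- *Study setting* lists an Asian-specific classification among the secondary aims.
- *Strengths and limitations* concedes that few participants may progress, and gives reduced power as the consequence.

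**The concern.** When the same events choose the predictors, shape the stages and supply the stage rates, the contrasts between stages look sharper than they would in new people. The fewer the events per candidate predictor, the larger this optimism.

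It is a different problem from low power. Low power hides real predictors, whereas optimism makes noise look like separation. A single p<0.05 rule applied across many candidates, genetic and metabolomic features included, adds false predictors to those that feed the framework. At stake is the credibility of an Asian-specific classification, which is a stated aim of the study.

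**Working it through.** **Inputs.** N = 1,500 and the rate of 0.51% are from *Sample size*. The candidates are from *Statistical methods*: three non-imaging groups plus eight imaging items make 11. Counting age, gender and race singly (*Data collection, examinations, and imaging*) makes 3 + 1 + 1 + 8 = 13. This is a low count, because several items have more than one level or measure in Table 3, and the number of genetic and metabolomic features is not given. The article states no event count, power or precision, so there is no figure of its own to reproduce.

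**Events.** At the cited rate, 1,500 × 0.0051 = 7.65 (Poisson 95% range 3 to 13). Read as an annual rate over 5 years, 1,500 × [1 − (1 − 0.0051)^5] = 37.9. Because the expected rate is not quantified, multiples of 0.51% are used as a range.

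**Optimism.** The simulation is a logistic model with N = 1,500, 13 independent normal predictors all fitted together, one outcome per person, a near-zero ridge for convergence and 100 runs per setting. True AUC and calibration slope come from a large fresh sample. Three predictors are real, with log odds ratio 0.5 per SD (an assumption).

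| Multiple of 0.51% | Events | Events per predictor (11) | Events per predictor (13) | Apparent AUC | True AUC | Calibration slope |
|---|---|---|---|---|---|---|
| 1 | 7.65 | 0.70 | 0.59 | 0.87 | 0.61 | 0.25 |
| 3 | 22.95 | 2.09 | 1.77 | 0.80 | 0.68 | 0.56 |
| 5 | 38.25 | 3.48 | 2.94 | 0.77 | 0.69 | 0.67 |
| 17 | 130.05 | 11.82 | 10.00 | 0.74 | 0.71 | 0.86 |

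With no real predictor at all, apparent AUC is 0.83, 0.71, 0.66 and 0.59 in the same order, against a true 0.50. The last row shows where the problem becomes small: ten events per predictor, a conventional yardstick, needs 130 events. That is 130/1,500 = 8.7%, or 17 times the cited rate.

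**False positives.** For 13 independent null tests at 0.05, the chance of at least one false positive is 1 − 0.95^13 = 49% (43% for 11). For m null genetic or metabolomic features the expected number is 0.05m. The article gives no m, so no count is claimed.

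**The case against.** A reader might infer that the plan expects 8 events, will fit 13 predictors to them and will therefore report badly over-optimistic results. The documents do not support that reading.

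- The 0.51% is a reference rate from a younger population with no stated period, and the article expects to exceed it.
- The predictors are candidates that may be included. There is no commitment to one model holding all of them.
- The framework is worded permissively and the integrated models are called exploratory.
- Nor does the article say that its referral thresholds, a separate secondary aim, would be derived from these models.

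The opposing case goes further. The sentence on stage rates promises descriptive rates, which may include transitions before late AMD with more events; it promises no AUC. Some predictors are known to be real, so an all-noise simulation is too harsh. Eye-level analysis adds second-eye events. Penalisation and validation are commonly left to an analysis plan, which is not shown here.

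Most of this limits the size of the problem without removing it. AUC is a gauge of optimism in the model behind the stages and is not the quantity promised. The table therefore uses three real predictors. Second-eye events are correlated and add little information. Blood sampling is optional, so the genetic and metabolomic analyses can have no more events than the whole cohort.

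The appeal to an unseen analysis plan does not settle it, because two of the elements are stated rules: p<0.05 for all tests, and the reporting of stage rates with a classification informed by the same cohort. The admission in *Strengths and limitations* covers power only.

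**Conclusion.** The concern holds in a bounded form. Followed as written, the plan gives optimistic stage contrasts and apparent discrimination across the plausible range of event counts. The optimism is severe near 8 events (0.87 against 0.61) and still material near 38 (0.77 against 0.69).

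These sizes assume that 13 candidates are fitted together, that three have the assumed effect, and that predictors are independent with one outcome per person. A smaller final model would reduce the optimism; selecting that model by p-value in the same data would bring some of it back. About 8 is a low-end count and should not be read as the study's expectation. Rates of transition into earlier stages could be better supported, but the article gives nothing from which to count them.

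**What to change.** 1. In *Sample size*, give the expected late-AMD events as a range (about 8 at the cited rate, about 38 at five times that rate) and state the period that 0.51% covers.
2. In *Statistical methods*, fit the multivariable discrete-time model with shrinkage (for example Firth or ridge). Limit predictors to a list ordered in advance, with its length tied to the observed number of events.
3. For genetic and metabolomic screening, replace the blanket p<0.05 rule with false-discovery-rate control.
4. In *Grading of retinal imaging and outcomes to be measured*, report stage progression rates first under an existing AMD classification. Report rates and discrimination for any newly derived stages only with bootstrap optimism correction that repeats predictor selection and cut-point choice, labelled exploratory pending external validation.

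The cost is wording and computing time. Fewer predictors will be declared and the stage contrasts will look less favourable. *Timeline of the study* reports 64 participants recruited so far, so the change can be made before most outcomes accrue.

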### Statistical methods

Descriptive statistics will be used to summarize baseline demographic, systemic, ocular, and imaging characteristics of the study cohort. Continuous variables will be presented as mean ± standard deviation (SD) for normally distributed data, or median and interquartile range (IQR) for non-normally distributed data. Categorical variables will be summarized using frequencies and percentages. Normality will be assessed using histograms and the Shapiro–Wilk test.

All analyses will primarily be performed at the eye level. As both eyes from a participant may be included, inter-eye correlation will be accounted for using generalized estimating equations (GEE) or mixed-effects models where appropriate.

Because AMD progression will be assessed at scheduled study visits rather than continuously observed, the primary analysis will evaluate progression to late AMD over predefined follow-up intervals using discrete-time survival models. Standard Cox proportional hazards models may be performed as sensitivity analyses. Where appropriate, interval-censored survival models will be explored.

Variables considered for multivariable models may include demographic factors, systemic risk factors, smoking history, and multimodal imaging biomarkers, including drusen characteristics, pigmentary abnormalities, subretinal drusenoid deposits, hyperreflective foci, drusen volume, double-layer signs, OCTA flow abnormalities, and choroidal parameters. Hazard ratios (HR) and 95% confidence intervals (CI) will be reported.

Longitudinal continuous imaging parameters, including drusen volume, retinal thickness, and choroidal thickness, will be analyzed using linear mixed-effects models to account for repeated measurements over time and within-subject correlation. Logistic regression analyses may additionally be performed for binary outcomes such as conversion to late AMD within predefined follow-up intervals.

Where appropriate, exploratory multivariable models integrating these biomarkers may be constructed to investigate risk stratification. All statistical analyses will be performed using R software (R Foundation for Statistical Computing, Vienna, Austria) and/or IBM SPSS Statistics (IBM Corp., Armonk, NY, USA). All statistical tests will be two-sided, and a p-value <0.05 will be considered statistically significant.

### Safety measurements

The risks associated with participating in this study are minimal. Both eye examinations and blood collection are routine procedures that form part of standard medical care, posing no additional risk to participants.

While most eye examinations are non-invasive, minimal risks may arise during imaging procedures such as CFP, OCT, and OCTA, including mild discomfort due to light exposure during retinal imaging. Clinical examinations are part of the standard of care, with detailed instructions and comfortable environments to help alleviate any unease associated with these procedures.

Blood sample collection is also minimally invasive, with minor risks such as temporary pain, bruising, or infection at the venipuncture site. This collection will align with standard care practices.

Pupil dilation is a common ophthalmic procedure. While it is generally safe, there are potential risks and side effects that should be communicated to patients. There is a very small risk of angle closure glaucoma (an acute rise in eye pressure) from the administration of eye drops. This risk is estimated to be about 1 in 5,000 people. There is also a risk of a mild local allergic reaction to the eye drop. If participants develop these adverse effects (red painful eye, blurry vision, nausea and vomiting), they will be referred for immediate and appropriate treatment at Singapore National Eye Centre (SNEC).

### Data management and confidentiality of data and patient records

Research data will be coded, participants will be de-identified, and the master list will be encrypted with a password. Only delegated study team members/ personnel authorized by PI will be allowed access to patient data.

All collected samples will be processed in the laboratory in a de-identified manner to ensure participant confidentiality.

### Timeline of the study

The project received approval from the CIRB in October 2025. Up to the time of manuscript submission, two community screening events had been conducted (18/10/2025 and 06/06/2026), and a total of 64 participants had been recruited. We anticipate recruitment to be completed by Jun 2027, 5-year follow-up by August 2032, and grading and data analysis by the last quarter of 2032.

### Oversight, monitoring, and amendments

PRIME study is part of the Translational Asian Age-related Macular Degeneration Program (TAAP). This project has 4 different themes, which altogether are aimed at elucidating the mechanisms behind AMD in order to cultivate diagnostics, develop novel therapies and tools to better understand the impact of the disease from the patients’ perspective. TAAP projects are monitored by Scientific Advisory Board (SAB) annually.

All protocol amendments will be submitted by the principal investigator to the CIRB. Once approval is obtained, team members will be notified of the changes made, and the new protocol will be followed. All amendments will be included in the subsequent publications.

## Discussion

AMD is the most common cause of irreversible blindness in elderly in developed countries [11]. Given the chronic nature of the disease and the need for long-term management, AMD imposes a substantial burden on healthcare systems worldwide. Despite its clinical importance, there is a lack of data on the progression of AMD and optimal screening protocol. Identifying individuals at risk of progression to advanced AMD is essential for timely intervention.

Previous studies investigating AMD progression have been limited by retrospective design or relatively short follow-up periods [12–14]. Although several prospective longitudinal studies have recently been reported, those cohorts were predominantly composed of Caucasians and have been conducted on patients with clinically diagnosed AMD [15–18]. Consequently, the natural history and biomarkers of AMD progression in Asian populations remain incompletely understood.

The proposed approach marks the first large Asian AMD dataset aimed at understanding the natural progression of this disease. By integrating a comprehensive multimodal retinal imaging with clinical, genetic and metabolic data, this longitudinal cohort will contribute to the development of future screening and risk stratification frameworks.

### Strengths and limitations

The major strengths of this study include its prospective longitudinal design, five-year follow-up period, substantial sample size, and comprehensive multimodal phenotyping alongside clinical and genetic data.

Several limitations should also be acknowledged. First, pupil dilation will not be performed during the baseline community-based screening visit, which may reduce the gradability of some fundus photographs. Second, information on lifestyle and environmental factors, including dietary habits, physical activity, sunlight exposure, educational attainment, and socioeconomic status, will not be collected, limiting the ability to assess their contribution to disease progression. Finally, the number of participants who progress to late AMD during the study period may be limited, which could affect the statistical power of some analyses. Continued follow-up of this cohort beyond five years may help address this limitation and provide additional insights into the long-term natural history of AMD.

### Dissemination plans

Study results will be published in peer-reviewed academic journals and will be presented at national and international congresses.
